# Test Schedule

| Treatment Cycle | Pre- registration | ≤14 days prior to  regist- ration | Active Monitoring Phase | | | | | |
| --- | --- | --- | --- | --- | --- | --- | --- | --- |
|  |  |  | Cycles 1-4^1^ | | | | Day 1 Subsequent cycles [21- day cycle] | At confirmed disease progression^2^ |
| Tests and procedures |  |  | C1D8 (±1  day) | C2D1 (±3  days) | C3D1 (±3  days) | C4D1 (±3  days) | (± 3 days) |  |
| HLA Class I Typing^R^ |  | X |  |  |  |  |  |  |
| ECOG performance status |  | X | X | X | X | X | X | X |
| History, physical exam, vital signs^3^, and weight |  | X | X | X | X | X | X | X |
| Child Pugh Score |  | X |  | X | X | X | X | X |
| Height |  | X |  |  |  |  |  |  |
| Adverse event assessment |  | X | X | X | X | X | X | X |
| Urine Pregnancy test |  | X4 |  |  |  |  |  |  |
| CBC with Differential:^5^ |  | X6 | X | X | X | X | X | X |
| Chemistry group: AST, ALT,  Bilirubin (total and direct), Creatinine, albumin, INR, LDH |  | X6 | X | X | X | X | X | X |
| TSH |  | X7 |  |  | X |  | X7 | X |
| Tumor imaging and measurement ^,8^ |  | X8 |  |  |  |  | X9 | X |
| Research blood specimens (see Section 14.0)^10,R^ |  | X | X | X | X | X | X10 | X |
| Tissue specimens (see Section 17.0)^,R^ | X11 |  |  |  |  |  | X12 | X12 |
| BRAF V600E and V600K  mutation testing |  | X |  |  |  |  |  |  |

- - 1. Cycle 1= 28 day, Subsequent Cycles=21 days.
    2. Confirmed progression is an objective status of progression on two consecutive evaluations at least 6 weeks apart.
    3. Vital signs must include blood pressure and heart rate.
    4. For women of childbearing potential only. Must be done ≤7 days prior to registration.
    5. CBC differential must include hemoglobin, platelets, absolute neutrophil count, absolute lymphocyte count, and absolute monocyte count
    6. CBC with differential and chemistry groups must be done ≤14 days prior to registration.
    7. TSH testing is to be performed ≤14 days prior to registration. And at the end of each even numbered cycle ( 2, 4, 6, 8, 10, etc.) until confirmed progression. If TSH is abnormal, T3 and free T4 testing should be performed.
    8. The initial tumor imaging (either CT or MRI, with preference for CT) will be performed ≤28 days prior to registration. The same imaging technique will be used in a patient throughout the study. If an excisional biopsy of a target lesion is to be done, baseline tumor imaging must be performed after the biopsy is done.

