# Treatment Evaluation Using RECIST Guideline

- 1. Requirements

The first scan after treatment initiation will be performed at the completion of Cycle 4 and will be then performed at the complete of every other cycle of treatment until disease progression is confirmed or 12 cycles of treatment have been administered without a confirmed disease progression (that is, imaging is to be done at the end of Cycles 4, 6, 8, 10, and 12). If a patient has not had disease progression after Cycle 12, subsequent scans will take place at the end of every 3^rd^ cycle of treatment thereafter (that is, at the end of Cycle 15, 18, 21 until confirmed disease progression)

Disease progression for this protocol is defined as meeting the RECIST criteria for disease progression on two consecutive evaluations at least 6 weeks apart.

- 1. Definitions of Measurable and Non-Measurable Disease
  2. Measurable Disease
  3. A non-nodal lesion is considered measurable if its longest diameter can be accurately measured as ≥1.0 cm with CT scan, CT component of a PET/CT, or MRI.
  4. A malignant lymph node is considered measurable if its short axis is

>1.5 cm when assessed by CT scan (CT scan slice thickness recommended to be no greater than 5 mm).

**NOTE:** *Tumor lesions in a previously irradiated area are not considered measurable disease.*

- 1. Non-Measurable Disease

All other lesions (or sites of disease) are considered non-measurable disease, including pathological nodes (those with a short axis ≥1.0 to <1.5 cm). Bone lesions, leptomeningeal disease, ascites, pleural/pericardial effusions, lymphangitis cutis/pulmonis, inflammatory breast disease, and abdominal masses (not followed by CT or MRI), are considered as non-measurable as well.

**NOTE:** ‘Cystic lesions’ thought to represent cystic metastases can be considered as measurable lesions, if they meet the definition of measurability described above. However, if non-cystic lesions are present in the same patient, these are preferred for selection as target lesions.

Lymph nodes that have a short axis <1.0 cm are considered non- pathological (i.e., normal) and should not be recorded or followed.

- 1. Guidelines for Evaluation of Measurable Disease
  2. Measurement Methods:
- All measurements should be recorded in metric notation (i.e., decimal fractions of centimeters) using a ruler or calipers.

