2. See Section 11.32 for details in regards to the requirements for PD via FDG-PET imaging.
   1. Overall Objective Status

The overall objective status for an evaluation is determined by combining the patient’s status on target lesions, target lymph nodes, non-target lesions, non- target lymph nodes, and new disease as defined in the following table:

| **Target Lesions & Target Lymph Nodes** | **Non-Target Lesions & Non-Target Lymph Nodes** | **New**  **Sites of Disease** | **Overall Objective Status** |
| --- | --- | --- | --- |
| CR | CR | No | CR |
| CR | Non-CR/Non-PD | No | PR |
| PR | CR  Non-CR/Non-PD | No | PR |
| CR/PR | Not All Evaluated* | No | PR |
| SD | CR  Non-CR/Non-PD Not All Evaluated* | No | SD |

| **Target Lesions & Target Lymph Nodes** | **Non-Target Lesions & Non-Target Lymph Nodes** | **New**  **Sites of Disease** | **Overall Objective Status** |
| --- | --- | --- | --- |
| Not all Evaluated | CR  Non-CR/Non-PD Not All Evaluated* | No | Not Evaluated (NE) |
| PD | Unequivocal PD CR  Non-CR/Non-PD  Not All Evaluated* | Yes or No | PD |
| CR/PR/SD/PD/Not all Evaluated | Unequivocal PD | Yes or No | PD |
| CR/PR/SD/PD/Not all Evaluated | CR  Non-CR/Non-PD Not All Evaluated* | Yes | PD |

*See Section 11.431

- 1. Symptomatic Deterioration

Patients with global deterioration of health status requiring discontinuation of treatment without objective evidence of disease progression at that time, and not either related to study treatment or other medical conditions, should be reported as PD due to “symptomatic deterioration.” Every effort should be made to document the objective progression even after discontinuation of treatment due to symptomatic deterioration. A patient is classified as having PD due to “symptomatic deterioration” if any of the following occur that are not either related to study treatment or other medical conditions:

- - - Weight loss >10% of body weight.
    - Worsening of tumor-related symptoms.
    - Decline in performance status of >1 level on ECOG scale.

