# Treatment/Follow–up Decision at Evaluation of Patient

- 1. Continuation of therapy

Patients who have not had disease progression and have experienced acceptable toxicity are to continue treatment per protocol until confirmed PD, unacceptable toxicity or refusal. And then they will go to event monitoring where patient and disease status will be reported every 6 months until death or a maximum of 5 years post-registration.

- 1. Progressive disease

The first instance in which a patient’s disease status meets the RECIST criteria for PD will continue two additional cycles of treatment per protocol and then undergo disease revaluation. If the initial documented progression is not confirmed by this scan, patients will continue treatment per protocol. If the initial documented progression is confirmed by this scan, patients will go to the event-monitoring phase where patient and disease status will be reported every 6 months until death or a maximum of 5 years post- registration. ***Exception: Patients who develop PD in the CNS should discontinue study treatment and go to Event Monitoring.***

- 1. For those on treatment at least one year and in complete response (CR)

At investigator’s discretion patients who have completed at least one year of protocol therapy and have had a complete response (CR) may discontinue all protocol therapy when the duration of the complete response has been at least 6 months (that is, at least 3 consecutive scans showing CR).

- 1. Discontinuation of protocol therapy

Criteria for discontinuation of protocol therapy include:

- - - Disease progression: Where disease progression is: the development of a new metastatic lesion or an objective status of disease progression (as defined by RECIST criteria) on two consecutive evaluations at least 6 weeks apart (section 13.2). ***Exception: Patients who develop PD in the CNS should discontinue study treatment.***
    - Request by patient to discontinue study treatment
    - Unacceptable toxicity
    - Intercurrent illness that would, in the judgment of the investigator, affect assessments of clinical status to a significant degree or require discontinuation of drug
    - Administration of radiotherapy, non-protocol chemotherapy, immunotherapy, biological agents, or an experimental drug during the trial
    - Development of new primary cancer
    - Ineligibility

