Patients who discontinue treatment due to progression or development of a second primary, desire for non-protocol treatment, intolerability, patient request, physician decision, or inter-current illness preventing further administration of protocol treatment will proceed to event monitoring phase of the trial where patient and disease status until death or a maximum of 5 years post-registration

- 1. Ineligible

A patient is deemed ineligible if after registration, it is determined that at the time of registration, the patient did not satisfy each and every eligibility criteria for study entry.

- - - If the patient received any protocol treatment, patient should discontinue study treatment and all data (except biospecimens) up until the point of discontinuation must be submitted. Patients will proceed to event monitoring phase of the trial where patient and disease status will be reported every 6 months until death or a maximum of 5 years post-registration.
    - If the patient never received any protocol treatment, on-study material (except biospecimens) and the End of Active Treatment/Cancel Notification Form must be submitted. No further No further data submission is necessary.
  1. Cancel

A patient who withdraws consent before any study treatment is given. On-study material (except biospecimens) and the End of Active Treatment/Cancel Notification Form must be submitted. No further data submission is necessary.

- 1. Treatment after PD

Subsequent treatment after confirmed PD is at the discretion of their attending physician.

- 1. PD in CNS

Patients who develop PD in the CNS only should discontinue study treatment and proceed to event monitoring phase of the trial where patient and disease status will be reported every 6 months until death or a maximum of 5 years post-registration.

MC1577 50 MCCC Amendment 8

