    - Dose Expansion Cohort: The endpoint is tumor response. Patients will be classified with respect to their best tumor response during treatment (e.g., CR, PR, SD, confirmed PD, Death, Too Early, or Not Evaluable). Estimates of tumor response and binomial confidence intervals will be reported. A patient whose tumor has meet the RECIST criteria for CR or PR on two consecutive evaluations at least 8 weeks apart is considered to have had a tumor response.

Adverse events: The maximum grade of each type of toxicity will be recorded for each patient. For each toxicity reported by dose level, the percentage of patients developing any degree of that toxicity as well as the percentage of patients developing a severe degree (Grade 3 or higher) will be determined.

Secondary end points include tumor response (for the Phase I/Dose Seeking Cohort), progression-free survival (PFS) and overall survival (OS) time: A patient whose tumor has meet the RECIST criteria for CR or PR on two consecutive evaluations at least 8 weeks apart is considered to have had a tumor response. Survival time is defined as the time from study entry to death due to any cause. Progression-free survival time is the time from study entry to the documentation of disease progression. If a patient dies

without a recurrence documented, the patient will be considered to have progressed on their death date.

All the study observations pertaining to adverse events, MTD, response, time to event points and laboratory correlates will be examined in an exploratory and hypothesis- generating fashion. The small sample size and the heterogeneous patient population associated with Phase I studies restricts the generalizability of the results. Any notable statistical finding will be viewed as an impetus for further study in Phase II trials rather than a definitive finding in and of itself.

- 1. Monitoring of the trial

This clinical trial will be monitored by the Mayo Clinic Cancer Center Data and Safety Monitoring Board (MCCC DSMB). The study statistician will prepare a report containing accrual and adverse event that will be submitted to MCCC DSMB every 3 months.

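### The PFS event and its date are undetermined for CNS progression and symptomatic deterioration, because the protocol's definitions of progression conflict

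*Protocol*

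**What the plan says.** **General rule.** Protocol Section 11.1: "Disease progression for this protocol is defined as meeting the RECIST criteria for disease progression on two consecutive evaluations at least 6 weeks apart". Section 4.0, footnote 2, repeats it: "Confirmed progression is an objective status of progression on two consecutive evaluations at least 6 weeks apart". Neither has an exception.

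**Ordinary path.** Under Section 13.2, a patient at first RECIST PD "will continue two additional cycles of treatment per protocol and then undergo disease revaluation". The second assessment is therefore built in.

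**CNS path.** Section 13.2 makes an exception: "Patients who develop PD in the CNS should discontinue study treatment and go to Event Monitoring". Section 13.4 repeats the stop of treatment, and Section 13.8 says of CNS-only disease: "Patients who develop PD in the CNS only should discontinue study treatment and proceed to event monitoring phase of the trial". Event monitoring collects patient and disease status every 6 months, for up to 5 years from registration. None of these sections orders a confirming scan.

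**Symptomatic deterioration.** Section 11 has this reported and classified as PD, for a decline "requiring discontinuation of treatment without objective evidence of disease progression at that time". It also asks sites to try to document objective progression afterwards.

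**Another definition.** Section 13.4, on stopping therapy, reads: "Where disease progression is: the development of a new metastatic lesion or an objective status of disease progression", the latter on two evaluations.

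**Endpoint.** Section 16.6: "Progression-free survival time is the time from study entry to the documentation of disease progression". A patient who dies with no recurrence on record is counted at the death date. The best-response categories, introduced as examples, include PD only in its confirmed form.

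**The concern.** A definition that needs two RECIST assessments cannot be met at the time by a patient who leaves treatment at the first one, or by a patient whose PD is not a RECIST finding at all. Section 11.1 makes that definition protocol-wide, while Sections 13.2, 13.4 and 13.8 and the symptomatic-deterioration text act on a single observation. Section 16.6 does not say which governs PFS.

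The choice matters because these patients have plainly failed treatment. If the strict rule is applied, their event moves to a later recorded progression or to death, and PFS is overstated. Duration of response, a secondary goal in Section 2, is exposed in the same way if it ends at progression. With so few patients, how two or three are classified can move the median, and the choice would otherwise be made after the data are seen.

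**Working it through.** **1. The definitions side by side**

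| Place in protocol | What counts as progression | CNS PD | Symptomatic deterioration |
|---|---|---|---|
| 11.1; 4.0 footnote 2 | RECIST PD at two assessments, 6+ weeks apart | Not met at first PD | Not met (no RECIST finding) |
| Symptomatic Deterioration text, Section 11 | Clinical decline, no objective evidence | n/a | Met at once |
| 13.4 | New metastatic lesion, or two-assessment PD | Met at once for a new lesion, read literally; not for growth of a treated one | Not addressed |
| 16.6 (PFS) | Documented progression; rule and date not stated | Undetermined | Undetermined |

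Growth of a known lesion can arise, because exclusion 3.29d admits patients with treated, inactive brain metastases. On the ordinary path the confirming assessment comes 2 x 21 = 42 days, or 6 weeks, after first PD. The CNS path has no counterpart.

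**2. Size of the effect (illustration only)**

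The protocol gives no PFS design figure to reproduce.

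From the protocol:
- median PFS of 22 weeks on pembrolizumab alone (Section 1);
- end of cycle 4 at 28 + 3 x 21 = 91 days = week 13;
- later scans at weeks 19, 25, 31 and 37, then every 9 weeks.

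Assumed:
- exponential time to PD, with PD dated at the next scan;
- a share q = 10-30% of patients whose first PD is CNS or symptomatic;
- exponential survival after that PD, with median s = 13-52 weeks;
- all other PD dated at first detection.

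*Baseline.* S(t) = 2^(-t/22), so S(13) = 0.664, S(19) = 0.550, S(25) = 0.455. Half have progressed first at the week-25 scan, so the median is 25 weeks. The 26-week PFS rate is about 45%.

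*Strict rule, counted at death.* The shares detected at weeks 13, 19 and 25 are 0.336, 0.114 and 0.095. Then

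26-week PFS = 0.455 + q[0.336 x 2^(-13/s) + 0.114 x 2^(-7/s) + 0.095 x 2^(-1/s)]

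- q = 0.1, s = 13: 0.455 + 0.1(0.168 + 0.079 + 0.090) = 0.489.
- q = 0.3, s = 52: 0.455 + 0.3(0.283 + 0.104 + 0.093) = 0.599.

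Median at the same two corners:
- q = 0.1, s = 13: just after week 25, PFS is 0.455 + 0.1(0.177 + 0.083 + 0.095) = 0.490. This is below one half, so the median stays at 25.
- q = 0.3, s = 52: just before week 37, PFS is 0.377 + 0.3(0.244 + 0.090 + 0.081 + 0.072) = 0.523. At the week-37 scan it falls to 0.312 + 0.3(0.487 + 0.065) = 0.477. The median is 37.

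Simulation of 400,000 patients agrees: median 25 to 37 weeks, 26-week PFS about 49% to 60%.

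*Without rounding to scans* (true median 22 weeks, s = 26-52): about 25 weeks at q = 10%, 27-29 at 20%, 31-33 at 30%.

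*Strict rule, but progression recorded at a status report 26 weeks after PD.* The earliest such report is week 13 + 26 = 39, later than every figure on the scan schedule, so they do not change. Without scan rounding the medians are about 25, 27-28 and 29-31 weeks. An earlier report would shrink the shift.

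*Counted at first documentation.* No shift.

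**3. Number of patients.** Section 16.4 allows at most 23 patients overall and 16 at the MTD. Ten to 30% is 2.3 to 6.9 of 23, or 1.6 to 4.8 of 16.

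**The case against.** The strongest reply is that the protocol can be read so that no bias arises. Section 16.6 speaks of documentation, not confirmation. Section 13.2 itself calls the first, unconfirmed PD documented progression, and the FDG-PET rule in Section 11 dates PD to the first abnormal scan. Section 13.4 lists a new metastatic lesion, which would cover a new brain metastasis. Symptomatic deterioration is expressly PD, by a specific rule set beside the general one. Disease status is still reported every 6 months, and Section 18 asks for supporting documents on progression after therapy.

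Much of this stands. A reader might infer that these patients can never meet the definition and are counted only at death. The text does not support that: it follows only if 11.1 is applied strictly in 16.6 and no later progression is recorded. Nor can one say that they have no best-response category, since that list is only illustrative. An upward bias in duration of response cannot be derived either, since 16.6 gives no end rule for it.

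What the reply does not remove is the conflict. Section 11.1 defines the very term that 16.6 uses. Section 13.4 governs stopping therapy rather than the endpoint, and its new-lesion clause misses growth of treated brain metastases. The request to document objective progression after symptomatic deterioration sets no scan or date. Event dating is often left to the SAP, but here the protocol already states rules that disagree.

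**Conclusion.** The point holds as a conflict between stated definitions. For CNS PD and symptomatic deterioration, the PFS event and its date depend on which section is followed. The symptomatic-deterioration half is the weaker one, because the text calls it PD outright.

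The effect runs from none, if first documentation counts, to a median of up to 37 weeks instead of 25 under the strict rule. The upper figure rests on assumed shares and survival times that the protocol does not give, and on exponential times. It illustrates the direction and order of the shift and is not a forecast.

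The consequence is limited. PFS is secondary, Section 16.6 calls the analyses exploratory, and no decision rule uses PFS. The MTD and the primary tumor-response rule are unaffected. The protocol should be clarified, but the conflict does not undermine the trial's main conclusions.

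**What to change.** Reconcile Section 11.1, the Symptomatic Deterioration text, Section 13.4 and Section 16.6 so that one definition of progression serves the endpoint. In 11.1 and 16.6 state that, for PFS, and for duration of response where it ends at progression:

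- CNS PD is an event on the date it is first documented, without confirmation;
- symptomatic deterioration as defined in Section 11 is an event on the date it is first documented, without confirmation;
- the two-assessment rule stays for all other PD.

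Let the PD category of best response include these two kinds of event.

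This takes a few sentences and no new data, and it changes no treatment rule. The cost is a slightly shorter reported PFS than the strict reading would give.

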# Body Fluid Biospecimens

- 1. Summary Table of Research Blood and Body Fluid Specimens to be Collected for this Protocol

| **Correlative Study**  **(Section 14.2 for more information)** | **Mandatory or Optional** | **Blood or Body Fluid**  **being Collected** | **Type of Collection**  **Tube (color of tube top)** | **Volume to collect per tube (# of**  **tubes to be collected)** | **After consenting to pre- registration**  **phase** | **Cycle 1,**  **Day 8 (±1day)** | **All other cycles*, Day 1**  **(±3 days)** | **At**  **confirmed progression** | **Process at site?**  **(Yes or No)** | **Temperature Conditions for Storage**  **/Shipping** |
| --- | --- | --- | --- | --- | --- | --- | --- | --- | --- | --- |
| Th1/Th2 polarity assays, immunophenotyping assays, plasma cytokine assays, and T cell and myeloid- derived suppressor cells (MDSCs) functional assays | Mandatory | Plasma, Peripheral blood mononuclear cells (PBMCs),  and whole blood | Sodium Heparin (Green) | 10 mL(7) | X | X | X | X | Yes | Ambient for initial transport, frozen liquid nitrogen for storage |
|  | Mandatory | Plasma, Peripheral blood mononuclear cells (PBMCs),  and whole blood | EDTA  (Pink) | 6mL (1) | X | X | X | X | Yes | Ambient for initial transport, frozen liquid nitrogen for storage |

^*^C2-C4, then at the beginning of each cycle when tumor imaging is performed. Please see table in Section 4.0, research blood specimen.

- 1. Collection and Processing

Peripheral blood will be collected in green top Vacutainer tubes. A special study refer card will be generated to identify these specimens. The samples will be kept at room temperature until processing. Blood samples will be collected at the clinical phlebotomy areas in the Mayo Clinic.

Seventy-six mL of collected blood will be sent in an expedited fashion to [name] laboratory c/o [name]. Samples will be processed within 12 hours of receipt.

Blood samples will be layered onto Ficoll and centrifuged to isolate plasma and peripheral blood mononuclear cells (PBMCs). Isolated plasma and cells will be frozen at

-80 °C and in liquid nitrogen, respectively, for later use.

The six mL EDTA collected whole blood will be sent in an expedited fashion to [name] lab. Blood samples will be immediately used for designed correlative studies in Human Cellular Therapy Lab.

| Samples to be collected | Peripheral whole blood (70 mL) |
| --- | --- |
| Tubes for collection | Green top Vacutainer tubes |
| Location for collection | Clinical phlebotomy areas in the Mayo Clinic |
| Delivery for processing | At room temperature |
|  | [name] lab, GU-323 |
|  | c/o [name] |
| Nature of processing | Ficoll centrifugation within 12 hours of receipt |
| Storage after processing | Liquid Nitrogen (PBMCs), -80 °C (plasma) |

| Samples to be collected | Peripheral whole blood (6 mL) |
| --- | --- |
| Tubes for collection | Pink top Vacutainer tubes |
| Location for collection | Clinical phlebotomy areas in the Mayo Clinic |
| Delivery for processing | At room temperature |
|  | Human Cellular Therapy Lab (Hilton 2) |
|  | c/o [name] |
| Nature of processing | Immediate processing per research experiment |
| Storage after processing | N/A |

- 1. Background and Methodology
  2. Th1/Th2 polarity assays

Frozen PBMCs from pre-treatment, post-cycle 1, and post-cycle 2 will be thawed and cultured for four hours with paramagnetic beads (Dynal, Oslo, Norway) coated with anti-CD3 and anti-CD28 antibodies (R and D Systems Minneapolis, MN). Following stimulation, cultured cells will be assessed via flow cytometry by measuring intracellular interferon gamma and interleukin (IL)-4. Brefeldin A will be purchased from Sigma-Aldrich (St. Louis, MO). Fluorochrome-labeled antibodies to IFNγ, IL-4, CD8, CD4, CD14, CD16, and CD19 will be purchased from Becton Dickinson (San Jose, CA). The stained samples will be analyzed by flow cytometry (FACScan and CellQuest software, Becton-Dickinson).

- 1. Immunophenotyping assays

The systemic impact of ibrutinib and pembrolizumab on immune cell subsets will be ascertained by immunophenotypic analysis of frozen PBMC for subsets of T helper cells, macrophages, and DC. To do this, we will label PBMC with antibodies to CD3, CD4, CD11c, CD14, C16, CD19, CD123, CD197, CD206,

CD294, HLA-DR, (BD Biosciences, San Jose, CA) and TIM-3 (R&D Systems, Inc., Minneapolis, MN). Immunophenotyping will be performed using manufacturer’s instruction in batch samples of the same patients analyzed on the same day. The stained samples will be analyzed by flow cytometry (FACScan and CellQuest software (BD Biosciences, San Jose, CA). Samples will be

assessed for the ratio of Th1 to Th2 cells (CD4+TIM-3+/CD4+CD294+), DC1 to DC2 cells (CD3-CD14-CD16-CD19-HLADR+CD11c+ to CD3-CD14-CD16- CD19-HLADR+CD123-), and M1 to M2 cells (CD14+CD197+ to

CD14+CD206+). Changes in Th1/Th2 ratio, DC1/DC2 ratio, and M1/M2 ratio between the pre-treatment sample and each other sample will be used to determine the systemic impact of treatment on immune cell subsets.

- 1. Plasma cytokine assay

We will profile the plasma cytokine changes as a result of vaccine administration. The BioRad human 27-plex cytokine panel will be used (Cat # 171-A11127, Bio-Rad, San Diego CA) for the measurements of plasma concentrations of IL-1β, IL-1rα, IL-2, IL-4, IL-5, IL-6, IL-7, IL-8, IL-9, IL-10, IL-12(p70), IL-13, IL-15, IL-17, basic FGF, eotaxin, G-CSF, GM-CSF, IFN-γ,

IP-10, MCP-1, MIP-1α, MIP-1β, PDGF, RANTES, TNF-α, and VEGF. The

assay will be performed as per the manufacturer’s directions. Briefly, 100 mcL of Bio-Plex assay buffer will be added to each well of a MultiScreen MABVN 1.2 um microfiltration plate followed by the addition of 50 mcL of the multiplex bead preparation. Following washing of the beads with the addition of 100 mcL of wash buffer, 50 mcL of the samples or the standards will be added to each well and incubated with shaking for 30 minutes at room temperature. The plasma (1:3 dilution) and standards will be diluted using the Bio-Plex human serum diluent kit and plated in duplicate. Standard curves will be generated with a mixture of 27 cytokine standards and eight serial dilutions ranging from 0-32,000 pg/mL. The plate will then be washed 3 times followed by incubation of each well in 25 mcL of pre-mixed detection antibodies for 30 minutes with shaking.

The plate will further be washed and 50 mcL of streptavidin solution were added to each well and incubated for 10 minutes at room temperature with shaking. The beads will be given a final washing and resuspension in 125 UL of Bio-Plex assay buffer. Cytokine levels in the sera will be quantified by analyzing 100 mcL of each well on a Bio-Plex using Bio-Plex Manager software version 4.0. Normal values for plasma cytokine concentrations were generated by analyzing 30 plasma samples from healthy donors (blood donors at the Mayo Clinic Dept. of Transfusion Medicine). A set of five normal plasma samples (standards) will be run alongside all batches of plasma analysis in this study. If the cytokine concentrations of the “standard” samples differ by more than 20%, results will be rejected and the plasma samples re-analyzed.

- 1. Tetramer assays

We will compare pre- and post-treatment frequencies of melanoma-specific CD8 T cells via tetramer staining in HLA-A2-positive patients. PBMCs will be labeled with HLA-A2 tetramers complexed with melanoma-associated antigen peptides (MART-127-35, GP100209-217, survivin-- ELTLGEFLKL, and tyrosinase368-376), and control peptides. PBMCs will be counterstained with anti-CD8 (BD Biosciences, San Jose, CA). The stained samples will be analyzed by flow cytometry (FACScan and CellQuest software, Becton-Dickinson).

- 1. T cell functional assays

One biopsy core from a pre-treatment metastatic lesion will be assessed for core volume (length of core x 3.14 x radius^2^) and percent tumor cells. The core will then undergo freeze thaw to make a tumor cell lysate. PBMCs will be sorted using CD14 antibody-coated beads. CD14+ cells will be cultured with GM-CSF and IL-4 for 5 days to make immature DCs (iDCs). The iDCs will be cultured with tumor lysates or media (negative control) and maturation factors to make loaded and unloaded mature DCs (mDCs). The loaded and unloaded mDCs will be incubated with CD14- cells. ELIspot assays for IFNg will be performed for CD4 and CD8 T cells.

- 1. Peripheral blood T cell Bim levels

PBMCs will be labeled with antibodies to CD8, CD11a, PD-1, and intracellular BIM. BIM levels will be quantitated in tumor-related (CD8+CD11a+PD-1+) cells. BIM levels will be compared in pre-versus post-treatment cells.

- 1. Characterization of tumor-infiltrating leukocytes

Tumor biopsy cores will be fixed in formalin and embedded in paraffin, then sectioned for immunohistochemistry (IHC). Sections will be stained for CD4, CD8, FoxP3, CD20, PD-1, and PD-L1. The number of cells bearing each marker will be quantitated.

